### Sample Size

The sample will consist of 20 triads comprising the patient, their radiation oncologist, and their general practitioner, for a total of 35 to 45 participants. A total of 10 patients will be from the Wollongong Cancer Centre (ie, regional) and 10 will be from the Shoalhaven Cancer Centre (ie, rural).

Sample size guidelines for qualitative interviews suggest that a range between 20 and 30 interviews is adequate for each group to reach data saturation [34]. The sample size for the quantitative level of agreement data requires a minimum of 5 samples; however, to increase the confidence interval, a higher sample is required [35].

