#### Qualitative Data

At pre- and postimplementation, participants (ie, patients, general practitioners, and radiation oncologists) will participate in semistructured interviews following a topic guide about radiotherapy follow-up care and their experience of shared care. Demographic data will be collected for all participants (ie, age, sex, level of education, and working years). The interviews will be audio-recorded and transcribed verbatim in preparation for thematic analysis in NVivo (QSR International).

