#### Qualitative Data

Thematic analysis is a commonly used analytical approach for qualitative data in implementation studies [39]. This involves mapping the transcribed data and emergent themes onto a priori domains. The themes will be compared across the regional and rural sites (ie, Wollongong and Shoalhaven) and triangulated between radiation oncologists, patients, and general practitioners.

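### The benchmark of 20 to 30 interviews per group is not delivered for all three participant types by 35 to 45 participants, except under counting conditions the protocol does not state

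*Protocol article*

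**What the plan says.** The Sample Size section sets the design: "The sample will consist of 20 triads comprising the patient, their radiation oncologist, and their general practitioner", "for a total of 35 to 45 participants". It divides the 20 patients equally between the regional and the rural centre. It does not say how many of the remaining participants are general practitioners and how many are radiation oncologists.

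The next paragraph gives the only support for the qualitative sample: guidelines that "suggest that a range between 20 and 30 interviews is adequate for each group to reach data saturation". It defines neither the group nor the way interviews are to be counted.

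Two other sections bear on the reading. Under Data Collection, Qualitative Data: "At pre- and postimplementation, participants (ie, patients, general practitioners, and radiation oncologists) will participate in semistructured interviews". Under Data Analyses, Qualitative Data, the themes are to be "triangulated between radiation oncologists, patients, and general practitioners". The natural reading of *each group* is therefore participant type, of which there are three, and each person is interviewed twice.

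**The concern.** The benchmark is stated per group, but the sample is stated only as a total. Once the 20 patients are taken out, the clinicians left look too few to fill two further groups of 20.

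This matters because feasibility and acceptability among patients, general practitioners and radiation oncologists is the study's stated aim, and the interviews are the data described for acceptability. A reader of the Sample Size section would take it that saturation is supported in every group. If one clinician group turns out to be small, conclusions about acceptability to that profession would rest on a justification that does not cover it. The Limitations section mentions participant numbers only for the agreement analysis, so the article does not acknowledge this gap.

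**Working it through.** **Inputs**
- Patients: 10 + 10 = 20 (Sample Size).
- Total participants T: 35 to 45 (Sample Size).
- Benchmark: 20 to 30 interviews per group (Sample Size).
- Interview rounds: 2, pre- and postimplementation (Data Collection, Qualitative Data).
- Groups: 3 participant types (Data Analyses, Qualitative Data).

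The check assumes that every planned participant gives every planned interview.

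**The plan's own total.** Twenty triads with no shared clinicians would be 3 × 20 = 60 people. A total of 35 to 45 is consistent with 20 triads if clinicians appear in more than one triad. It cannot be derived, because the split between clinician types is not given.

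**Clinicians available.** C = T − 20, so 35 − 20 = 15 to 45 − 20 = 25, for both professions together.

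**Counting people, or one round.**
- Three groups of 20 need 3 × 20 = 60, against at most 45.
- The patient group has 20 and just meets the lower bound.
- The two clinician groups need 2 × 20 = 40, against 15 to 25.
- The smaller clinician group is largest under an even split: C/2 rounded down, which is 7 at T = 35 and 12 at T = 45.
- At T = 40 or below there are at most 20 clinicians, and at least one belongs to each profession. Neither clinician group can then reach 20.
- As an illustration, if all 20 general practitioners were different people, radiation oncologists would number at most 45 − 20 − 20 = 5.

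**Counting both rounds together.**
- All interviews: 2 × 35 = 70 to 2 × 45 = 90, against 3 × 20 = 60 to 3 × 30 = 90. The overall count looks sufficient.
- Patients take 2 × 20 = 40 of these. Clinicians give 2 × 15 = 30 to 2 × 25 = 50, against 40 needed.
- Twenty interviews in each clinician group need at least 10 people in each, so C ≥ 20 and T ≥ 40.

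| Total T | Clinicians C | Most interviews possible in the smaller clinician group (both rounds) | Splits giving at least 20 in each |
|---|---|---|---|
| 35 | 15 | 14 | none |
| 36 | 16 | 16 | none |
| 37 | 17 | 16 | none |
| 38 | 18 | 18 | none |
| 39 | 19 | 18 | none |
| 40 | 20 | 20 | 10/10 only |
| 41 | 21 | 20 | 10/11 or 11/10 |
| 42 | 22 | 22 | 10/12 to 12/10 |
| 43 | 23 | 22 | 10/13 to 13/10 |
| 44 | 24 | 24 | 10/14 to 14/10 |
| 45 | 25 | 24 | 10/15 to 15/10 |

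No split works at five of the eleven planned totals (35 to 39). At the other six, at least 10 radiation oncologists leave at most 20 − 10 = 10 to 25 − 10 = 15 general practitioners for 20 patients, so several patients would have to share one. The Recruitment section has each consenting patient's own general practitioner invited and plans no sharing. In the illustrative split of 20 general practitioners and 5 radiation oncologists, the radiation oncologists give 2 × 5 = 10 interviews, half the lower bound.

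**The case against.** The strongest reply is that the benchmark counts interviews, not people. Everyone is interviewed twice, so 70 to 90 interviews are planned, against 60 to 90 for three groups of 20 to 30. This stands in part: with both rounds pooled, 20 per group is reachable at totals of 40 to 45 when each clinician group has at least 10 members. A reader might infer that the benchmark can never be met and that the justification is simply false. The article does not support that, because it does not rule out pooling and does not give the clinician split.

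It is also fair to say that the cited guidance only suggests what is adequate, and that the article nowhere promises 20 interviews in each group. The guidance itself is not at hand, so its own unit cannot be checked. Nor is *group* defined. If it meant site, and participants divided evenly between sites (an assumption), two rounds would give 70/2 = 35 to 90/2 = 45 interviews per site. Participant type remains the more natural reading, since the analysis triangulates across types.

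Two further inferences should not be drawn. One is that the rounds cannot be pooled because they cover different subjects; the article describes one topic guide and does not say that its content changes between rounds. The other is that the regional-rural comparison also fails the benchmark. The analysis section says only that "The themes will be compared across the regional and rural sites" and attaches no saturation or sample-size claim to this.

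What the reply does not remove is the failure at totals of 35 to 39, the dependence on at least 10 people in each clinician group, and the double counting of the same informants. A second interview adds material, but not another clinician's viewpoint.

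**Conclusion.** The point holds in a conditional form. The stated benchmark does not support the planned sample for all three participant types across the planned range. Counted as people or within one round, at least one clinician group falls short at every total, with at most 7 to 12 in the smaller group. With both rounds pooled, the benchmark is unreachable at 35 to 39 participants. At 40 to 45 it is reachable only with at least 10 general practitioners and at least 10 radiation oncologists.

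This rests on reading *group* as participant type and on complete interviews from everyone; losses would only lower the counts. The patient group meets the lower bound on either count, with 20 in one round and 40 over both. The defect lies in the justification. It does not show that the interviews will be uninformative, or that either clinician group will in fact fail to reach saturation.

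**What to change.** Restate the qualitative justification in the Sample Size section:

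1. Define *group* as participant type, if that is what is meant, and state the counting unit: people or interviews, one round or both.
2. Give the expected numbers of general practitioners and radiation oncologists within the total of 35 to 45.
3. Claim the 20 to 30 benchmark only for patients and for any clinician group whose expected number meets it under that unit. If rounds are pooled, say that repeat interviews of the same person are counted separately.
4. For any group below the benchmark, make no saturation claim in advance and report the saturation observed.

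No change to recruitment, interviews or analysis is needed. The cost is a slightly less favourable justification.

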### Recruitment

The radiation oncologists will review their follow-up clinic lists from both sites and screen for initial inclusion criteria. The researcher will invite each patient to participate via a postal letter on behalf of the radiation oncologist. Once each patient consents to participate, their general practitioner will be invited. General practitioners will be eligible for continuing professional development points for participating. If the general practitioners do not consent to participate, the patient will not be eligible.

### Implementation

The foundation of this shared cancer follow-up model of care is that clinician communication exchange is two-way and in real time, while the radiation oncologist continues to oversee the follow-up care. The model includes real-time transfer of results, internal system alerts, and rapid referral to address any issues that may arise. During this study, patients maintain their current specialist standard follow-up care, with all relevant specialists, and will continue follow-up care with their radiation oncologist upon completion of the study.

General practitioners will complete a standardized online radiation oncology course developed by the Cancer Institute New South Wales [36]. The course developed for health professionals addresses the principles of radiation therapy, patient assessment grading systems of side effects, and supportive care management. General practitioners will receive one-on-one training by a radiation oncologist that includes localized radiotherapy-specific follow-up care, a review of the recruited patient’s treatment background, and a demonstration of the clinical follow-up assessment that the general practitioner will use in the patient's follow-up review.

### Data Collection

#### Overview

The PROsaiq software will be used to administer clinical assessments. The assessments were compiled internally at the ISLHD for follow-up of radiotherapy patients. These clinical assessments review physical items on a scale from 0 to 4 for items specific to radiotherapy follow-up care, such as pain, fatigue, physical performance, bowel issues, urinary issues, and appetite (see Table 1). The included scales were sourced from the Radiation Therapy Oncology Group scales [37] and the Common Terminology Criteria for Adverse Events, version 3.0 [38].

**Table 1 table1:** Radiation oncology follow-up standardized clinical assessment.

Tumor type	Clinical assessments
Breast	Fatigue, ECOG (Eastern Cooperative Oncology Group) Performance Status, appetite, weight loss, chest and breast pain, telangiectasia, lymphedema-related fibrosis, and disease state (ie, local, regional, or distant)
Colorectal	Fatigue, ECOG Performance Status, appetite, weight loss, proctitis, pelvic pain, vomiting, and diarrhea
Prostate	Fatigue, ECOG Performance Status, erectile dysfunction, dysuria, and rectal hemorrhage

#### Quantitative Data

The quantitative data will be collected from Phase 1. The radiation oncologist will enter the clinical assessment directly into the oncology information system, while the general practitioners will enter the clinical assessment on the webpage link that will be provided to the general practitioner. Both sets of data from these clinical assessments will be stored in the hospital oncology information system.

#### Qualitative Data

At pre- and postimplementation, participants (ie, patients, general practitioners, and radiation oncologists) will participate in semistructured interviews following a topic guide about radiotherapy follow-up care and their experience of shared care. Demographic data will be collected for all participants (ie, age, sex, level of education, and working years). The interviews will be audio-recorded and transcribed verbatim in preparation for thematic analysis in NVivo (QSR International).

### Data Analyses

#### Quantitative Data

The clinical assessment data will be extracted from the oncology information system; the Cohen κ value and percent agreement for each variable from Table 1 will determine the level of agreement between general practitioners and radiation oncologists. The agreement will assess the concordance between two measurements of each variable with the expectation that there will be near-perfect agreement on each item (>0.81). The results of the analysis and level of agreement will be presented to the general practitioners and radiation oncologists to guide any additional education and training.

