### Limitations

Possible limitations of this research are the number of participants needed to determine the level of agreement; the research team will monitor this. Another limitation identified is that the general practitioners and radiation oncologists recruited may assess the same oncological patients from a different viewpoint due to differences in training. The researcher will assist in the coordination of appointments and try to minimize the impact on the patients and health professionals.

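### Plain Cohen κ and percent agreement on 0 to 4 grades show which items agree poorly, but not the size or direction of the disagreement

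*Protocol article*

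**What the plan says.** All references are to the protocol article.

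- **Scale.** Data Collection, Overview: "These clinical assessments review physical items on a scale from 0 to 4 for items specific to radiotherapy follow-up care". Table 1 lists the items by tumour type. One breast item is categorical and not clearly a severity grade: "disease state (ie, local, regional, or distant".
- **Measures.** Data Analyses, Quantitative Data: "the Cohen κ value and percent agreement for each variable from Table 1 will determine the level of agreement". No other agreement measure is named, and weights are not mentioned.
- **Benchmark.** The same paragraph sets agreement per item "with the expectation that there will be near-perfect agreement on each item (>0.81".
- **Use.** The results go back to both groups of clinicians "to guide any additional education and training". Study Design adds that Phase 1 informs what GPs need to be taught, and that the agreement shown is meant to reassure both sides that the GP can do the review reliably.
- **Possible difference between raters.** Limitations notes that the two groups "may assess the same oncological patients from a different viewpoint due to differences in training".
- **Size.** Sample Size gives 20 triads, so at most 20 GP-oncologist pairs per item.

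**The concern.** Unweighted κ and percent agreement treat every mismatch alike. A GP who records 1 where the oncologist records 0 counts the same as a GP who records 4 where the oncologist records 0. Both measures are also symmetric in the raters: exchanging GP and oncologist leaves them unchanged, so a tendency to grade low looks the same as a tendency to grade high.

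For the two stated uses, size and direction are a large part of what the reader needs. Training differs according to whether GPs are one grade out or miss severe effects, and whether they tend to under-grade or over-grade. Reassurance that a GP can do the review depends on the same two facts. A single benchmark of 0.81 adds to the difficulty, because the value of κ depends on the weights and the text does not fix them.

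**Working it through.** The document gives no computed agreement figure, so there is nothing to reproduce. The check uses constructed tables of 20 pairs (the number of triads in Sample Size) on the 0 to 4 scale. **The cell counts are assumptions.** The document gives no expected distribution of grades.

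**Formula.** κ = 1 − D_obs / D_exp. D_obs is the mean of d over the observed pairs, and D_exp is its mean under independent margins. For unweighted κ, d = 1 for any mismatch. For linear weights, d = |i − j| / 4. Pairs are written (oncologist, GP).

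**Size of disagreement**

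*Example A:* (0,0)×10, (1,1)×4, (4,4)×2, (0,1)×4.
- Agreement 16/20 = 80%.
- Chance agreement (14×10 + 4×8 + 2×2)/400 = 176/400 = 0.44.
- Unweighted κ = (0.80 − 0.44)/0.56 = 0.643.
- Linear: D_obs = 4×0.25/20 = 0.05; D_exp = (28 + 28 + 10 + 6 + 20 + 12)/400 = 104/400 = 0.26; κ = 1 − 0.05/0.26 = 0.808.

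*Example B:* as A with grades 1 and 4 exchanged: (0,0)×10, (4,4)×4, (1,1)×2, (0,4)×4.
- Agreement and chance agreement are unchanged (80%, 0.44), so unweighted κ is again 0.643.
- Linear: D_obs = 4×1/20 = 0.20; D_exp = (112 + 7 + 40 + 6 + 5 + 12)/400 = 182/400 = 0.455; κ = 1 − 0.20/0.455 = 0.560.

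| | Agreement | Unweighted κ | Linear κ | Quadratic κ |
|---|---|---|---|---|
| A: four 0-versus-1 | 80% | 0.643 | 0.808 | 0.930 |
| B: four 0-versus-4 | 80% | 0.643 | 0.560 | 0.525 |

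The two measures that the protocol names cannot tell A from B.

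**The benchmark need not follow severity.** Take (0,0)×12, (1,1)×4, (2,2)×2 and two GP under-gradings; agreement is 90% either way.
- Two (1,0) pairs: chance agreement (12×14 + 6×4 + 2×2)/400 = 0.49; κ = 0.41/0.51 = 0.804, below 0.81. Linear κ 0.844.
- Two (4,0) pairs: chance agreement (12×14 + 4×4 + 2×2)/400 = 0.47; κ = 0.43/0.53 = 0.811, just above 0.81. Linear κ 0.565.

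The margin is tiny, but the ordering is the wrong way round.

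**Direction.** Transposing Example A turns four GP over-gradings into four under-gradings. Agreement stays at 80% and κ at 0.643, and linear and quadratic κ stay at 0.808 and 0.930. Only the cross-table separates the two: four pairs with the GP higher, or four with the GP lower.

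**Where weighting has no effect.** If an item's ratings use only two grades, every mismatch has the same d. It cancels from D_obs/D_exp, and weighted and unweighted κ are identical.

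**Effect on the benchmark.** With grades used evenly (four pairs each) and four one-grade mismatches that leave the margins even, unweighted κ = (0.80 − 0.20)/0.80 = 0.75 and linear κ = 1 − 0.05/0.40 = 0.875. The same data fall below 0.81 on one coefficient and above it on the other.

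**The case against.** The strongest case on the other side has six parts.

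1. *The text does not say unweighted.* That is right. It is the ordinary reading of the bare term, and an analysis plan that is not shown could set weights. What remains is that the article names the deciding measures and attaches a numerical benchmark, whose meaning changes with the weights.
2. *The measures do guide training.* A reader might infer that they are useless for that purpose. The document does not support this: results are given per item and so show where the raters differ, and both gradings are stored in the hospital system, so size and direction can be recovered. The measures serve the purpose partly.
3. *The protocol expects GPs to grade differently.* A reader might infer this from Limitations. That passage says only that the viewpoints may differ, and it gives no direction. The stated expectation is near-perfect agreement.
4. *The examples are extreme.* This stands as a limit on size. Eligibility Criteria takes patients due for their 3-year review and excludes suspected or confirmed recurrence, so grade 4 may be rare, and items rated only on two grades are unaffected by weighting. Moreover, only fatigue and ECOG status appear for all three tumour types in Table 1, so other items will have fewer than 20 pairs if all three types are recruited.
5. *No patient decision rests on κ.* Correct. The oncologist also reviews the patient in Phase 1 and is alerted to the GP's results in Phase 2, usual specialist follow-up continues, and no stop or go rule is attached to the coefficient. The point concerns interpretation, and the documents do not support a claim of harm.
6. *Weighted κ is also blind to direction, and the choice of weights is a judgement.* Both are true. Hence the cross-table is needed as well, and the weights should be fixed in advance.

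**Conclusion.** The point holds in a limited form. On the ordinary reading, the only agreement measures named for the 0 to 4 items show which items agree poorly, but not by how much or in which direction. They therefore meet the training and reassurance aims incompletely.

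The possible size is shown by Examples A and B, where identical reported results conceal a gap in linear-weighted κ of 0.808 − 0.560 = 0.248. This rests on assumed tables of 20 pairs that include severe grades. The gap in real data could be much smaller, and is nil for items rated on two grades. The blindness to direction does not depend on the grade distribution.

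The weakness limits what Phase 1 can tell its users. It does not invalidate the study, and it can be put right in the analysis wording.

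**What to change.** 1. For the items graded 0 to 4, prespecify linear-weighted κ as the main coefficient, with unweighted κ and percent agreement reported alongside. Linear weights count each grade of distance equally; the choice matters less than fixing it before the data are seen.
2. Keep unweighted κ for disease state, if it is recorded as nominal categories.
3. State which coefficient the >0.81 expectation applies to, and reconsider whether 0.81 is still the intended level. Weighting raises κ when errors are one grade, so a silent change of coefficient could loosen the benchmark.
4. For each item, report the GP-by-oncologist cross-table with the number of pairs in which the GP grade is lower and the number in which it is higher, and how many of each differ by 2 or more grades. Counts avoid treating the grades as interval data.
5. Include these tables and counts in the feedback to GPs and radiation oncologists.

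Cost: slightly more reporting, and the benchmark must be restated. Both sets of assessments are already stored in the oncology information system, so no further data, patients or visits are needed.

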#### Qualitative Data

Thematic analysis is a commonly used analytical approach for qualitative data in implementation studies [39]. This involves mapping the transcribed data and emergent themes onto a priori domains. The themes will be compared across the regional and rural sites (ie, Wollongong and Shoalhaven) and triangulated between radiation oncologists, patients, and general practitioners.

